#### Process Evaluation

3.5.3

We will carry out a process evaluation in the month following the intervention at each participating site as outlined below.

To address RQ6, implementation will be measured using the following dimensions of RE‐AIM (https://re-aim.org/) (alongside effectiveness measures described as part of the primary evaluation) [67]:
Reach: Percentage of the target population who participate, and differences in demographics between people who do participate and those of the overall target population (e.g., age, sex, cognitive functioning).Adoption: Percentage of staff invited who participate, and characteristics of long‐term care workers participants versus nonparticipating staff (e.g., role, years of experience).Implementation: Record of adaptations made to the SSI during the study, and long‐term care workers' adherence to intervention components (e.g., completion of sensory champion tasks, attendance at training sessions).

Perceived acceptability of the intervention will be evaluated using a combination of a post‐intervention survey and individual, structured interviews with a subsample of approximately 20 participating long‐term care workers. The survey and interview topic guide will be informed by the Theoretical Framework of Acceptability [68, 69].

Mechanisms of impact (RQ7) will be explored using individual, semi‐structured, in‐depth interviews conducted by the sensory Lead Therapist, a speech pathologist with experience in conducting qualitative interviews. These interviews will involve a subsample of approximately 20 participating long‐term care workers to understand the extent to which the SSI achieved behaviour change via the mechanisms proposed in our earlier behavioural analysis (e.g., our intervention resulted in improved knowledge of (1) how to insert hearing aids, (2) who uses hearing/vision devices, which subsequently results in increased use of day‐to‐day device management).

Contextual influences (RQ8) will be explored using a written log maintained by the Sensory Champion(s) and individual, semi‐structured interviews at the conclusion of the study. The contextual domains, as defined by the Context and Implementation of Complex Interventions (CICI) framework [70] include: geographical (e.g., infrastructure, availability of resources); epidemiological (e.g., level of care needs within the long‐term care home, lockdowns due to disease outbreaks); socio‐cultural, ethical and legal (e.g., organisational culture, governance); socioeconomic (e.g., residents' access to hearing and vision services/devices); and political (e.g., policy changes, workforce issues, long‐term care home closures) domains.

### Data Analysis Plan

3.6

We will apply methods (e.g., Bonferroni correction) to control for family‐wise error rates for each research question. Data analysis will be conducted with SPSS [71].

Two generalised linear models will be applied to evaluate the impact of the SSI on the quality of life of residents and their informal caregivers. For both, the dependent variables will be the individual domains of quality of life (resident or informal caregiver) and the independent variable will be time. Potential covariates will include demographic variables, (resident) health status, (resident) cognitive and sensory functioning, (resident) use of hearing and vision devices and use of long‐term care workers' sensory support behaviours.

Paired *t*‐tests (or other repeated measures test) will be used to examine pre‐/post differences in long‐term care workers' use of sensory support behaviours.

A series of generalised linear models will be used to evaluate the impact of the SSI on residents' use of hearing/vision devices, quality of patient‐provider communication, well‐being, sensory function and behaviour. For each model, the independent variable will be time and potential covariates will include demographic variables, health status, cognitive and sensory functioning and use of long‐term care workers' sensory support behaviours.

Two generalised linear models will be applied to evaluate the impact of the SSI on informal caregivers' well‐being and relationship with the resident. For each model, the independent variable will be time. Potential covariates will include demographic variables, resident health status, resident cognitive and sensory functioning and use of long‐term care workers' sensory support behaviours. The nested structure of the data will be taken into consideration in the modelling.

To evaluate the cost‐effectiveness of the SS intervention compared to standard care (RQ5), we will report a within‐trial analysis, economic modelling and a budget impact analysis. The within‐trial analysis will include two components: (1) the health benefits associated with QoL outcomes for participants, as well as informal caregivers (RQ1), and (2) costs associated with intervention and healthcare resources using a micro‐costing study. We will estimate the intervention cost by recording the time spent by long‐term care workers on supporting residents' hearing and vision needs over 5 days, and extrapolate it over the relevant time horizon. Healthcare resource use will be measured at baseline and at a 3‐ and a 6‐month follow‐up using the Resource Utilisation in Dementia (RUD) Lite [72, 73], a standardised tool for collecting resource use data in dementia care. Since the tool was originally developed for community settings, only the section related to patient healthcare resource utilisation will be used to fit long‐term care settings. For informal caregivers, we will use the three sections of the RUD Lite concerning caregivers detailing primary caregiver description, time and work status.

Unit prices will be sourced from the corresponding Medicare Benefits Scheme items, Pharmaceutical Benefits Scheme items, the National Hospital Cost Data Collection [74] and other relevant sources.

We will estimate the lifetime cost‐effectiveness of the intervention using economic modelling (e.g., Markov modelling). We will conduct a literature review to inform the model structure and parameters not sourced from the intervention study. We will also report a budget impact analysis to determine the financial implications of implementing the SSI for the federal government. We will report the results of the cost‐effectiveness analyses according to the Consolidated Health Economic Evaluation Reporting Standards (CHEERS) checklist [75].

The economic evaluation outcome will be the incremental cost‐effectiveness ratio (ICER), which will determine whether the intervention is cost‐effective using Australia's implicit cost‐effectiveness threshold [76]. The ICER represents the incremental cost associated with a unit gain of health outcome of interest (e.g., a QALY) between two interventions.

The equation for the ICER is represented as:

$$\mathrm{ICER}=\frac{C_{1}-C_{0}}{E_{1}-E_{0}}$$
where *C*
_1_ and *C*
_0_ are the costs associated with the long‐term care model and the usual care, respectively, while *E*
_1_ and *E*
_0_ are the effectiveness estimates (QALYs) of the of the long‐term care model and the usual care, respectively. The numerator and denominator for the ICER calculation will be estimated using generalised linear models accounting for data distribution and covariates. Sampling uncertainty will be handled by nonparametric bootstrap sampling. Bootstrap iterations will be plotted in the cost‐effectiveness plane and cost‐effectiveness acceptability curves.

For the economic model, uncertainty around the lifetime cost‐effectiveness results will be explored using deterministic and probabilistic sensitivity analysis.

For the budget impact analysis, we will report the cost to the federal government in Australian dollars. We will estimate this cost to the Australian healthcare system using projected utilisation estimates of SSI in Australia in the long‐term care setting over a relevant time horizon.

RQ6‐8: Descriptive statistics will be used to examine reach, adoption, implementation and acceptability. The qualitative interviews will be transcribed verbatim and analysed using mixed deductive‐inductive thematic analysis [77] to explore (1) the acceptability of the intervention to residents, long‐term care workers and informal caregivers, (2) the mechanisms through which staff behaviour change occurred and (3) the impact of contextual factors on implementation. Coding frameworks will be developed a priori based on the Theoretical Framework of Acceptability [69], the Capability, Opportunity, and Motivation Model of Behaviour (COM‐B) [30, 31] and the CICI framework [70]. After thoroughly reading interview transcripts, meaning units will be assigned to the most appropriate theoretical construct after which subthemes will be identified inductively using Braun and Clarke's methodology [78]. Rigour will be enhanced through regular peer consensus meetings between two coders performing independent double coding and other members of the research team. Qualitative results will be reported in line with the consolidated criteria for reporting qualitative research (COREQ).

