### Sample Size Calculation

3.3

Approximately 87 residents will be recruited at baseline. The evaluation is powered to detect a standardised effect size of *d* = 0.3 (because hearing/vision interventions are associated with small‐to‐medium effects on health‐related quality of life outcomes in the primary treatment group (i.e., residents) [40, 41, 42]. Assuming a correlation of 0.6 between baseline and 12‐week follow‐up Health Utility Index‐3 (HUI‐3) scores and an attrition rate of 20% at follow‐up (a conservative estimate based on the 12%–15% rates observed in previous similar studies) we will need to recruit 87 residents at baseline to achieve 80% power to detect the effect size at the two‐sided 5% level of significance, according to estimates generated by G*Power software [43].

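### Bonferroni, given as an example, is the only multiplicity method named; Holm's step-down procedure would give the same family-wise protection and lose less power, mainly in the many-outcome RQ3 family

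*Protocol article*

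**What the plan says.** The Data Analysis Plan (section 3.6) opens with its only statement on multiplicity: "We will apply methods (e.g., Bonferroni correction) to control for", continuing "family‐wise error rates for each research question". Two things are settled by it: the error rate to be controlled is the family-wise one, and each research question is its own family. The method is left open, with Bonferroni as the one example.

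The same section analyses RQ3 (residents' device use, communication, well-being, sensory function and behaviour) with several generalised linear models, and RQ4 (informal caregivers) with two. Section 3.5.2 lists the RQ3 measures: hearing device use, vision device use, the IOI-HA, two PEECH subscales, an anxiety scale, a depression scale, a social isolation measure, a hearing handicap inventory, the LV-VFQ-20 and the NPI-NH. That makes 11, or 10 if device use counts once. Routine quality indicators come on top. RQ1 is also a multi-outcome family, because its dependent variables are the separate quality-of-life domains.

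The Sample Size Calculation (section 3.3) is made for "80% power to detect the effect size at the two‐sided 5% level of significance", with no adjustment for multiplicity.

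**The concern.** In a family of 11, Bonferroni tests every outcome at 0.05/11 = 0.0045. Holm starts at the same threshold for the smallest p-value, then relaxes it step by step (0.05/10, 0.05/9, and so on) for as long as hypotheses are rejected. It needs no extra assumption about dependence, keeps the family-wise error at or below 5%, and cannot reject fewer hypotheses than Bonferroni. So for the significance decision itself, plain Bonferroni has no advantage over Holm.

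At stake is power for the secondary outcomes. The trial has 80% power for a single comparison at an unadjusted 5% level, so a family of ten or more outcomes has little to spare. If several effects on communication, well-being or behaviour are real, Bonferroni would miss some that Holm would declare.

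**Working it through.** **Inputs from the article (section 3.3).** Effect size d = 0.3; "Assuming a correlation of 0.6 between baseline and 12‐week follow‐up Health Utility Index‐3 (HUI‐3) scores"; "an attrition rate of 20% at follow‐up"; two-sided 5%; 80% power; 87 residents at baseline.

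**Assumptions, because the article gives no figures.** RQ3 family size 10 or 11; each real secondary effect equal to d = 0.3; the HUI-3 correlation of 0.6 and the 20% attrition carried over to every secondary outcome; correlation between outcomes of 0, 0.3 or 0.5; a paired test in place of the planned generalised linear models; 5% per family.

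**Step 1: the article's own sample size.**
- Standardised paired effect: dz = 0.3/√(2 × (1 − 0.6)) = 0.3/√0.8 = 0.335.
- The exact noncentral t gives n = 72 completers (power 0.802). 72 × 1.2 = 86.4, rounded up to 87, which is the stated figure.
- The normal approximation gives (1.960 + 0.842)²/0.335² = 69.8, so 70 completers; 70/0.8 = 87.5, so 88.

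The figure reproduces. It contains no multiplicity adjustment, so the choice between Holm and Bonferroni does not alter it.

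**Step 2: completers.** 87 × 0.8 = 69.6, so 69 or 70.

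**Step 3: power of one outcome under Bonferroni (exact t).**
- Unadjusted 5%, n = 70: 79%.
- Two outcomes, level 0.025, n = 70: 70%.
- Ten outcomes, level 0.005, n = 69: 46%.
- Eleven outcomes, level 0.0045, n = 70: 45%.

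**Step 4: Bonferroni against Holm, by simulation.** Average power per true effect:

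| Family | Real effects | Bonferroni | Holm | Gain (points) |
|---|---|---|---|---|
| 11 outcomes | 1 | 45% | 45% | 0 |
| 11 outcomes | 5 | 45% | 48% | 3 |
| 11 outcomes | 8 | 45% | 51% | 6 |
| 11 outcomes | 11 | 45–46% | 56–57% | 11 |
| 2 outcomes (as in RQ4) | 1 | 70% | 70% | 0 |
| 2 outcomes (as in RQ4) | 2 | 70% | 76% | 6 |

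These rows use t-tests, n = 70, correlation 0.3 between outcomes and 20,000 replicates. A second run (family of 10, n = 69, normal approximation, correlation 0 or 0.5, 100,000 replicates) gives the same gains from a slightly higher base: 49–50% with both methods for one real effect, 49% to 52–53% for five, and 49% to 60% for ten. The base is higher because the normal approximation is a little optimistic against the exact t.

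In every replicate of both runs, Holm rejected all that Bonferroni rejected. Holm's family-wise error never exceeded 5%. In the second run, the chance of at least one true rejection differed by 0.002 or less between the two methods. Holm's benefit is therefore in declaring further effects once the first has been found.

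**The case against.** The strongest objection is that the article does not fix Bonferroni at all. The sentence speaks of methods in the plural and gives one as an example. Holm is a family-wise method and already fits that wording, and the final choice may stand in an analysis plan that is not shown. This is correct. A reader might infer that the trial has committed itself to Bonferroni for every research question and is already giving power away; the text does not support that. Power is lost only if plain Bonferroni is what is used. Nor does every question have a family to adjust: RQ5 is reported as an incremental cost-effectiveness ratio with bootstrap uncertainty, and RQ6 to RQ8 are descriptive or qualitative.

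The second objection is that the largest gain is the most favourable case. It needs every RQ3 effect to be real and of size d = 0.3. This also stands. The intervention acts on device use, communication and background noise together, so several real effects are plausible, but the article does not establish that.

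Third, the inputs come from the HUI-3 calculation and may not suit RQ3. The IOI-HA in particular is completed only by residents who own hearing aids. The Introduction cites 9% hearing-aid use in a European long-term care sample; if that applied here, about 0.09 × 70 = 6 residents would contribute. The planned models also have covariates and three time points. So the absolute powers are illustrative. The ordering of the two methods does not depend on any of these inputs.

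Finally, Bonferroni gives simple simultaneous confidence intervals that match its tests, and Holm does not. That is a genuine cost, and the only one found.

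**Conclusion.** The point holds as a small efficiency gain. Section 3.6 is not wrong: Bonferroni is valid and is only an example. If it is applied to RQ3, Holm would give the same protection with average power per true effect higher by about 0 points (one real effect), 3 points (about half real) or 10 to 11 points (all real). In RQ4 the range is 0 to about 6 points.

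These sizes rest on assumed family sizes, d = 0.3 for each real effect, r = 0.6, about 70 completers on every outcome and paired tests. The RQ4 figure borrows the residents' inputs, since the article gives none for caregivers. No figure was computed for RQ1 or RQ2. That Holm never rejects less than Bonferroni rests on no such assumption.

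A reader might go further and conclude that real effects will probably be reported as absent, or that the sample size is affected. Neither follows: the gain is close to nil when few effects are real, and the 87 residents were derived without any multiplicity adjustment.

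**What to change.** In section 3.6, replace the Bonferroni example with Holm's step-down procedure, applied within each research question that tests more than one outcome (RQ1 to RQ4). RQ1 should be included: limiting the change to the secondary questions would leave the primary, multi-domain family with no named method. Report Holm-adjusted p-values beside unadjusted confidence intervals, and label the intervals as unadjusted.

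The cost is one sentence and no change to sample size, data collection or models. The drawback is that simultaneous intervals matching Holm's decisions are less simple than Bonferroni intervals, so an unadjusted interval may exclude no effect where the adjusted p-value is above 0.05; the report should say so.

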#### Primary Outcome

3.5.1

Residents' quality of life will be measured using the interviewer‐administered versions of the HUI‐3 40Q [38] questionnaire with 1‐week recall, and the Quality of Life‐Aged Care Consumers (QOL‐ACC) [39] instrument. The HUI‐3 captures the sensory quality of life attributes and therefore will be more sensitive to the effect of the intervention. The interviewer‐administered version of the HUI‐3 was chosen as some participants will likely have mild cognitive impairment or dementia and therefore many may be unable to complete a self‐report measure. The QOL‐ACC will also be used to capture the quality of life as the HUI‐3 has shown inconsistencies in people with dementia. The QOL‐ACC has been validated both for people with dementia and people living in long‐term care [48] and is routinely collected by the Australian Government for long‐term care residents. We will measure QoL using both self‐assessed and proxy‐assessed versions of both HUI‐3 and QOL‐ACC to ensure completeness, where proxy‐assessment will be completed by the informal caregivers or long‐term care workers where an informal caregiver is not available. QOL‐ACC and HUI‐3 responses will be used to estimate utilities with an Australian algorithm [49, 50]. Utilities will be used to estimate quality‐adjusted life years (QALYs), which combine the utility of a health state with the time spent on that health state. QALYs will be used as the benefit measure in the cost‐effectiveness analyses. To capture the impact of the SSI on the duration of daily care delivery, a research assistant will use field notes to record the duration of daily care delivery based on direct observation of care workers entering and leaving the resident's room during baseline and post‐intervention periods.

Informal caregivers' quality of life will be evaluated using the 5‐item EQ‐5D‐5L [51], which evaluates five dimensions, including mobility, self‐care, usual activities, pain/discomfort and anxiety/depression. Higher scores reflect poorer quality of life. Utilities will be estimated using an Australian algorithm [51, 52].

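### The stated 80% power is for one HUI-3 comparison at an undivided 5%; it does not describe the domain-level, family-wise-controlled analysis planned for the primary question

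*Protocol article*

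**What the plan says.** Section 3.3 (Sample Size Calculation) gives the only power statement: "The evaluation is powered to detect a standardised effect size of *d* = 0.3", in residents. It assumes a correlation of 0.6 between baseline and 12-week HUI-3 scores and 20% attrition, and concludes that 87 residents are needed "to achieve 80% power to detect the effect size at the two‐sided 5% level of significance". It does not mention more than one test.

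Section 2 makes RQ1 a single question about the quality of life of both residents and informal caregivers. Section 3.5.1 (Primary Outcome) lists HUI-3 and QOL-ACC for residents and the five-dimension EQ-5D-5L for caregivers. It gives a reason for the second resident instrument: "The QOL‐ACC will also be used to capture the quality of life as the HUI‐3 has shown inconsistencies in people with dementia".

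Section 3.6 (Data Analysis Plan) sets the RQ1 analysis as two generalised linear models, one for residents and one for caregivers, in which "the dependent variables will be the individual domains of quality of life (resident or informal caregiver) and the independent variable will be time". It also states: "We will apply methods (e.g., Bonferroni correction) to control for family‐wise error rates for each research question".

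**The concern.** The level used to size the study is not the level that will be applied, and the quantity used to size it is not clearly the quantity that will be tested. Section 3.3 spends the whole 5% on one HUI-3 comparison. Section 3.6 spreads RQ1 over several domains, from more than one instrument and two participant groups, and then controls the family-wise error across them. Nothing in sections 3.3, 3.5.1 or 3.6 sets one score at one time point apart for the full 5%.

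This is the primary question, and 3.3 is the only power claim. A null result after correction could be read as a negative finding from a study with 80% power when the power for that test was lower. With no primary test named, the headline result could also be chosen after the domains have been seen.

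**Working it through.** **Inputs.** From section 3.3: d = 0.3, correlation r = 0.6, two-sided alpha 0.05, power 80%, attrition 20%, 87 residents. From section 3.6: family-wise control within RQ1, Bonferroni as the example. The number of RQ1 tests, K, is not stated. The only domain count the article gives for an RQ1 instrument is the five dimensions of EQ-5D-5L, in caregivers. K = 2 to 20 is therefore an assumed range.

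**Step 1: reproduce the 87.** For a paired t-test the standardised mean change is

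dz = d / √(2(1 − r)) = 0.3 / √0.8 = 0.3354.

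The exact noncentral t at two-sided 5% needs 72 completers (power 0.802), and 72 × 1.2 = 86.4, rounded up to 87. The stated figure is thus matched by one unadjusted paired test, with no multiplicity allowance. (Dividing by 1 − 0.2 instead would give 72 / 0.8 = 90. That difference is minor and not part of this point.)

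**Step 2: power at the corrected level.** Completers: 87 × 0.8 = 69.6, taken as 70. Noncentrality: 0.3354 × √70 = 2.806, with 69 degrees of freedom. Under Bonferroni each test is run at 0.05 / K. The table gives power for one given test, the d detectable with 80% power at 70 completers, and the residents to recruit for 80% power per test (completers needed / 0.8).

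| K | alpha per test | power per test | detectable d | recruits for 80% |
|---|---|---|---|---|
| 1 | 0.05 | 79.0% | 0.30 | 72 / 0.8 = 90 |
| 2 | 0.025 | 69.6% | 0.34 | 88 / 0.8 = 110 |
| 5 | 0.01 | 56.5% | 0.37 | 108 / 0.8 = 135 |
| 10 | 0.005 | 46.8% | 0.40 | 123 / 0.8 = 154 |
| 20 | 0.0025 | 37.8% | 0.43 | 138 / 0.8 = 173 |

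K = 2 is the mildest resident reading: one score each for HUI-3 and QOL-ACC. K = 10 and K = 20 only illustrate a domain-level family. Every row applies d = 0.3 and r = 0.6 to each test, although the article gives these values for residents and ties the correlation to HUI-3 alone.

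**Step 3: other family-wise methods.** I simulated 70 completers with every endpoint at d = 0.3 and change scores correlated 0 or 0.5 (my assumption). Average power per test under Holm was about 76% for K = 2, 67–69% for K = 5, 58–59% for K = 10 and 45–48% for K = 20. A fixed sequence that starts with HUI-3 tests it at the full 5% and keeps the 79%.

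**The case against.** The strongest reply is that the article does not commit to Bonferroni. The wording offers it as an example, and a fixed sequence is itself a family-wise method. A full protocol or analysis plan that is not shown could name such a sequence with HUI-3 first, and the power would then stand. This is right as far as it goes. A reader might infer that the stated power and the stated analysis cannot both hold under any method, and the text does not support that. What remains is that the article, as written, reserves the full 5% for nothing and makes the domains the dependent variables.

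Second, a reader might infer that a true d = 0.3 would more likely be missed than found. That holds only per test, under Bonferroni, with a family of about eight tests or more (power 49.8% at K = 8), and the article gives no count. Under Holm with ten tests, average power stays above one half if all endpoints move. The chance that at least one of ten Bonferroni tests is significant exceeds 90% in the same simulation.

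Third, the family could be smaller than it looks. With time as a factor, each outcome may get one overall test, so multiplying instruments by two follow-ups does not follow from the text.

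Fourth, two further readings go beyond the document. Section 3.3 speaks of HUI-3 scores and never says overall score, so it is an inference that a summary score was powered and then dropped. If domain scores were meant, an undivided 5% still does not match several domains under family-wise control. Section 3.3 also confines its effect size to residents and its correlation to HUI-3, so its inputs should not be used to put a power figure on caregiver EQ-5D-5L.

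**Conclusion.** The point holds in a limited form: the 80% in section 3.3 belongs to one HUI-3 test at an undivided 5%, and section 3.6 describes a different primary analysis. Under Bonferroni the loss is about 9 percentage points on the mildest resident reading (79% to 70% with two tests) and about 23 points with five tests (79.0% to 56.5%). The figures of 47% and 38% are illustrative worst cases, because the test count is undocumented and they apply per test under Bonferroni only. All the figures rest on 70 completers and on d = 0.3 and r = 0.6 holding for every test. They concern residents; the article gives no basis for a caregiver power figure. It is not established that the study is underpowered whatever method is chosen, since a HUI-3-led fixed sequence would preserve the stated power for HUI-3.

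**What to change.** In sections 3.3, 3.5.1 and 3.6, name one resident HUI-3 summary score at the 3-month follow-up as the single primary test at two-sided 5%, and state that this is the 12-week comparison used for sizing. Place the other RQ1 instruments after it in a pre-specified fixed sequence. The order is for the investigators to choose, bearing in mind their own remark on HUI-3 in people with dementia. Report the individual domains and the 6-month contrast as secondary estimates with confidence intervals.

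Alternatively, keep the domain-level family-wise analysis, state the number of tests and the method, and restate the power or the detectable effect at the corrected level.

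Either route is a change of wording and needs no extra participants. The first costs the domain-level results their confirmatory status. The second leaves a less favourable power statement.

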To evaluate the impact of the intervention on residents' use of hearing and vision devices, quality of resident‐provider communication, well‐being, sensory function and behaviour (RQ3), we will employ direct observation, self (or proxy) report questionnaires and professional caregiver report. The use of hearing and vision devices will be measured using direct observation and resident self‐report. Residents will complete the International Outcome Inventory‐Hearing Aids (IOI‐HA) if they own hearing aids [56]. Items on the IOI‐HA are scored on a 5‐point Likert scale from left (worst) to right (best), with higher scores representing better hearing aid outcomes. Resident‐provider communication will be measured using two subscales of the Patient Evaluation of Emotional Care During Hospitalisation (PEECH) questionnaire [57, 58] capturing ‘level of personal value’ (10 items) and ‘level of connection’ (3 items). Items are measured on a 4‐point scale (3 = all, 2 = most, 1 = some, 0 = none) with higher scores reflecting better patient‐provider communication. Overall well‐being will be measured using the 20‐item Geriatric Anxiety Inventory [59] and 8‐item Geriatric Depression Scale (nursing home version) [60]. Participants are asked to respond with yes/no to a series of statements that ask about symptoms of anxiety and depression. Functional and social impacts of hearing loss will be evaluated using the 5‐item Social Isolation Measure using an 11‐point Likert scale [61] and the 10‐item Revised Hearing Handicap Inventory—Screening (or proxy version) where each item is assigned a score of 4, 2 or 0 [62]. Both measures ask about the social and emotional impacts of hearing loss, with higher scores being indicative of more perceived hearing‐related activity limitations and participation restrictions. Vision function will be measured using the 20‐item Veterans Affairs Low Vision Visual Functioning Questionnaire–short form (LV‐VFQ‐20) (or proxy version) [63], which asks about the impact of corrected vision in four domains: reading, visual motor, visual information processing and mobility. Each item is measured on a 5‐item scale: ‘not difficult’, ‘slightly/moderately difficult’, ‘extremely difficult’, ‘impossible’ and ‘do not do it for nonvisual reasons’. The presence of responsive behaviours will be evaluated by professional care staff using the Neuropsychiatric Inventory–care home version (NPI‐NH) [64]. Lastly, routinely collected data pertaining to the National Aged Care Quality indicators (e.g., medication management, falls and major injury) will be extracted from participants' long‐term care records.

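### The models that estimate SSI impact as a time effect list, as potential covariates, variables the SSI is meant to change, without limiting them to baseline values

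*Protocol article*

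**What the plan says.** Section 3.6 (Data Analysis Plan) evaluates SSI impact on resident and caregiver quality of life (RQ1) with two generalised linear models in which time is the independent variable. There is one group and no control arm, so the time term is the only estimate of impact. The potential covariates are demographics, resident health status, resident cognitive and sensory functioning, and "resident) use of hearing and vision devices and use of long‐term care workers' sensory support behaviours". The models for RQ3 (resident secondary outcomes) and RQ4 (caregiver well-being and relationship) also list staff behaviours. They do not list device use.

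Elsewhere the article treats the same variables as targets or outcomes of the SSI:

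- Section 3.2 and Table 1 make three staff behaviours the direct target. The first is helping residents with their devices.
- Section 2 asks for SSI impact on staff behaviours (RQ2) and on residents' device use (RQ3).
- Section 3.5.2 (Secondary Outcomes) states: "The use of hearing and vision devices will be measured using direct observation and resident self‐report". It also reviews staff task lists at baseline and after the intervention.
- Section 3.5.3 (Process Evaluation) describes better staff knowledge, "which subsequently results in increased use of day‐to‐day device management".

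Section 3.3 gives the planning values: "Approximately 87 residents will be recruited at baseline" and "The evaluation is powered to detect a standardised effect size of *d* = 0.3".

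**The concern.** A covariate that lies between intervention and outcome absorbs the part of the effect that runs through it. If device use and staff behaviours enter the RQ1 model as measured at each visit, the time coefficient answers a different question: how much quality of life changed beyond what changes in device use and staff support explain. The primary question asks how much it changed in total.

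Staff behaviour is the sharper case. Adding sensory support items to the daily task list is itself an SSI component (Table 2), and task-list completion is one of the measures of staff behaviour. That covariate may largely switch on with the intervention and so be strongly collinear with time.

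Sensory functioning raises the same issue if it is entered after baseline. Sensory function is an RQ3 outcome, and section 3.5.1 says that the HUI-3 captures sensory attributes.

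At stake is the primary estimate. An SSI that improves quality of life mainly through better device use and staff support could be reported as having a small or absent effect.

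**Working it through.** **Inputs from section 3.3:** d = 0.3, pre-post correlation r = 0.6, two-sided 5%, 80% power, 20% attrition, 87 recruited. **Assumed, because the article gives no figure:** the mediated share (0% to 100%) and the shift in the mediator (0.5 or 1.0 SD).

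**1. The plan's own figure.** For a paired comparison, dz = d/√(2(1 − r)) = 0.3/√0.8 = 0.3354. The normal approximation gives n = ((1.960 + 0.842)/0.3354)² = 69.77 completers, and 69.77/0.80 = 87.2. The stated 87 reproduces. With 70 completers the exact paired-t power is 79.0%, which is the starting point below.

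**2. The time coefficient with mediators entered over time.** It becomes 0.3 × (1 − mediated share). Power at 70 completers follows from dz × (1 − share), so this step counts only the smaller coefficient:

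| Share mediated | Time coefficient | Power |
|---|---|---|
| 0% | 0.30 | 79% |
| 25% | 0.225 | 55% |
| 50% | 0.15 | 28% |
| 75% | 0.075 | 11% |
| 100% | 0 | 5% |

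**3. Collinearity with time.** Pre-post data were simulated for 70 residents, 3000 runs per cell. The mediator had SD 1, pre-post correlation 0.6 and a mean shift of 0.5 or 1.0 SD. Its coefficient on the outcome was share × 0.3/shift. The outcome change was regressed on an intercept (the time effect) plus one of: nothing, the mediator change, or the centred baseline mediator.

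| Share mediated | Adjusted coefficient (shift 0.5 / 1.0) | Power (shift 0.5 / 1.0) |
|---|---|---|
| 0% | 0.301 / 0.299 | 67% / 45% |
| 25% | 0.223 / 0.223 | 45% / 27% |
| 50% | 0.149 / 0.151 | 23% / 16% |
| 75% | 0.072 / 0.074 | 9% / 8% |
| 100% | 0.000 / −0.002 | 5% / 5% |

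The 0% row shows that power is lost even when nothing is mediated, because the covariate moves with time.

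**4. The same data without the problem.** With no covariate, the time effect was 0.293 to 0.301 and power 77% to 80%. With the baseline mediator only, it was 0.299 to 0.302 and power 77% to 81%. Baseline entry does no harm.

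**The case against.** The best reply is that the article fixes less than this. The covariates are called potential, their timing is not stated, and the final set may be settled in an analysis plan that is not shown. Baseline information exists for both: section 3.4.2 asks residents about their history of hearing and vision management, and section 3.5.2 reviews task lists and assesses staff skills at baseline. The sample size reproduces as an unadjusted paired comparison, and the Abstract mentions paired t-tests alongside generalised linear models for quality of life.

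Much of this stands, and it rules out several stronger readings:

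- A reader might infer that the models will certainly adjust for post-intervention values and so drive the estimate towards zero. The text permits that adjustment but does not require it.
- A reader might infer that an SSI working as designed would show no effect. That needs 100% mediation through these two variables. The sensory champion's room audits, information on pathways and referrals (Table 3) can act by other routes.
- A reader might infer that device use is a covariate throughout. It is listed for RQ1 only.
- A reader might take section 3.5.3 as stating a path from device management to quality of life. It concerns how knowledge changes staff behaviour, explored by interview. The case for a causal path rests on sections 2, 3.2 and 3.5.2.

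The reply does not remove the problem. Section 3.6 ties paired t-tests to staff behaviours only, names no total-effect model as primary, and does not limit these covariates to baseline. Describing them as potential leaves the choice between a total and a direct effect open in the primary analysis.

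**Conclusion.** The point holds in conditional form. Section 3.6 allows adjustment of the SSI effect for variables that the SSI is meant to change: device use in RQ1, and staff behaviours in RQ1, RQ3 and RQ4. If they enter after baseline, the time coefficient is a direct effect and does not answer the primary question.

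The size depends on the mediated share, which the documents do not give. At a share of one half, a true 0.30 is estimated as 0.15, and power falls from about 79% to about 28%, or 16% to 23% in the collinear scenarios. At full mediation, the extreme bound, the estimate is zero.

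The figures are for the resident comparison at an uncorrected 5% level with 70 completers. The direction assumes that better device use and staff support improve quality of life, which is the protocol's premise. If the authors intend baseline values only, there is no attenuation and the text only needs to say so.

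**What to change.** In section 3.6:

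1. Name the time effect from a model without post-intervention covariates as the primary estimate for RQ1, RQ3 and RQ4.
2. State that all covariates are baseline values. For residents these are demographics, time in care, level of care need, sensory screening and cognition. The caregiver models should also carry the caregivers' own demographics from section 3.4.1. Sensory functioning enters at baseline only. Baseline device use or staff behaviours may stay.
3. Remove post-intervention device use from the RQ1 list, and post-intervention staff behaviours from the RQ1, RQ3 and RQ4 lists.
4. If the mechanism is of interest, examine these variables in a separate analysis labelled as mediation, with its assumptions stated.

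This is a change of wording before analysis. It needs no new data, visits or participants.
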